### **3.7 Data collection**

The research project comprised three phases. In the first step, the education program and the instruments (knowledge on foot care and outcome expectation) will be developed by making use of the principles of Bandura's Social Cognitive Theory (SCT) with the emphasis on taking action to promote self-efficacy (van de Laar & van der Bijl 2001). The program materials; a questionnaire and the education program (to be given to the respondents) a diary/ folder (for the health staff in the RSK) and teaching folder and written instructions (for researcher) will be developed in this phase.

In the second step, the education program will be assessed in a pilot study, followed by implementation of main study. Lastly, evaluation process of the program will be assessed.

#### **3.7.1 Step 1: Development of the materials for the intervention program**

The several steps are undertaken for the development of the education program. The information will be gathered from local professional body/organization such as Malaysian Diabetes Association, National Diabetes Registry and National Diabetes Institute. Interviews with diabetic nurse educators, foot care nurse, and endocrinologist from hospitals/ clinics/ organisations to get information about foot diabetes education. Elderly with diabetes also will be interviewed to on the most common problem situations they experience in following diabetes foot self-care behaviour recommendations. Development the material of the program will be established such as follows:

- The questionnaire measuring on knowledge of foot care and foot care outcome expectation.
- The intervention module; teaching materials, pamphlet and instructions for the researcher.
- A checklist for respondent and health provider in the RSK. The checklist/ reminder will be used to monitor the foot self-care behaviour of the respondents.

The theoretical background of the education program is based from Albert Bandura's Self-efficacy theory. There a few components for enhancing the self-efficacy level such as mastery experience, modelling, supporting psychological states and verbal persuasion (Bandura, 1997). In this study, self-efficacy enhancing activities will be applied together with knowledge transfer and the researcher's approach. Knowledge transfer will be conducted during seminar, demonstration and follow up session to increase their knowledge and awareness. Self-efficacy enhancing activities will be stressed during and after the education session. A good researcher-respondents' relationship need to be established so that the respondents will trust and follow to the researcher's instruction. Respondents will be encouraged to establish a realistic goals on new targets (tailored action plan) in performing foot self-care behaviour. They need to start work in a small realistic steps so that they will be more focus, confidence and become motivated to perform the desired behaviour (mastery experience). Respondents will be given a daily reminder/ checklist and a hand-out

(symbolic modelling) so that they will perform the foot self-care behaviour daily. In order to maintain their confidence level, a positive feedback and strong encouragement need to be given continuously (verbal persuasion). During follow up, the researcher will discuss with respondents, sharing experience each other (social modelling) and get feedback on goals, examination of obstacles and problem situations (self-appraisal). The respondents will be advised to be more responsible in performing of foot self-care behaviour regularly and participate actively to the recommended lifestyle adjustments. Table 3.3 showed the integration of self-efficacy enhancing activities in the intervention phase.

Table 3.3 The integration of self-efficacy enhancing activities in the intervention phase

| Tasks                                | Self-efficacy enhancing activities                                                                                                                                                                                                                                                                                                                                                                                                                                                                                                                                                                                                                                                                         |
|--------------------------------------|------------------------------------------------------------------------------------------------------------------------------------------------------------------------------------------------------------------------------------------------------------------------------------------------------------------------------------------------------------------------------------------------------------------------------------------------------------------------------------------------------------------------------------------------------------------------------------------------------------------------------------------------------------------------------------------------------------|
| Knowledge transfer                   | 
 
• Oral information by care the researcher
 
• Written/ oral information in a slide and pamphlet
 
                                                                                                                                                                                                                                                                                                                                                                                                                                                                                                                                                   |
| Self-efficacy enhancement activities | 
 
• Establishing goals together with the respondent
 
• Agreement on new targets
 
• Working with small realistic steps
 
• Building up a relationship of trust with the respondent with attention being paid to difficult situations and obstacles
 
• The respondent starts to try the behaviour independently
 
• Positive feedback and encouragement
 
• The respondent keeps a daily reminder/ checklist
 
• Sharing experience each other
 
• Referring to hand-out for skills improvement
 
• Feedback on goals during consultation, examination of obstacles and problem situations
 
 |
| The researcher's approach            | 
 
• Leave responsibility to the patient
 
• Encourage an active role for the patient
 
• Recommendations on lifestyle adjustments for the patient
 
                                                                                                                                                                                                                                                                                                                                                                                                                                                                                            |

Subsequently, submission of the draft (questionnaire, education program, teaching materials and instructions and folder) for assessment to 6 content experts (people with practical experience (clinical areas) and theoretical knowledge (academician) in the field related to this study will be conducted. Besides, a pilot study (10% from total sample required) will be conducted to assess the validity and reliability as well as practicability and feasibility of the program.

After feedback from the expert persons and preliminary data obtained, the development of second draft of the materials (questionnaire, education program a folder, teaching folder and instructions) on the basis of a careful weighing of the comments of the content experts will be conducted.

### **3.7.2 Step 2: The intervention; the education program**

All the independent elderly who stayed in the RSK will be invited to participate in this study. The program will be carried for 12 weeks and consisted of a total of 4 visits: 1) to get preliminary data/ assessment, 2) the education program 3) Follow up and 4) evaluation. Figure 3.3 illustrated the flow chart of recruitment and the intervention program. Refer to Table 3.4 for the whole activities of the intervention program.

#### **1) Screening, assessment, consent approval and baseline data**

If the respondents agree to take part in this study they must take part in screening session. All of them will be screen for glucose level (Fasting Blood Sugar (FBS)).

Also, the respondents will be assessed for level of independence in activities of daily living. Respondents will be assessed with The Katz Index of Independence in Activities of Daily Living (ADL) (Katz et al., 1970; Shelkey, Mason, & Wallace, 2012). The instrument used to assess functional status as a measurement of the client's ability to perform activities of daily living independently (Meiner & Lueckenotte, 2006; Shelkey, Mason, & Wallace, 2012). A score of 6 indicates full function, 4 indicates moderate impairment, and 2 or less indicates severe functional impairment (Shelkey, Mason, & Wallace, 2012).

Subsequently, the respondents will be assessed for cognitive level and depression level. The reason of screening is therefore, to ensure that they are absent from cognitive impairment and depression. All respondent will be assessed for cognitive level with the Malay version of Elderly Cognitive Assessment Questionnaire (ECAQ) (MOH, 2007). The Malay ECAQ refers to 10 items divided into three parts which are memory (3 questions), orientation (six questions) and recall (1 question) (MOH, 2007). Maximum score is 10;  $\geq 7$  is normal, 5-6 borderline and  $\leq 4$  dementia (MOH, 2007). The Malay Geriatric Depression Scale (GDS) four items will be used to examine the depression level (MOH, 2007). At the cut-off point of  $\geq 2$  in detecting depression (MOH, 2007).

The respondents also will be excluded if they have been diagnosed with mental illness. The information about the disease will be gathered from health staff in the RSK. Otherwise, without this screening the performance of elderly (with mental health, dependence in ADL, cognitive impairment and depression) in foot self-care behaviour may influence the effectiveness of the program. These strategies are to minimise bias that may influence the effectiveness of the program and result findings.

The respondents are also will be informed on the study purpose verbally with the subject information sheet and the respondents also will be asked to give (signature or thumb print) an informed consent.

Baseline data (a set of questionnaire; demographic data, clinical characteristics, foot self-care behaviour (DFSBS), foot care efficacy expectation (FCCS), foot care outcome expectation (FCOE) knowledge on foot care (KFC) and quality of life (FS-QOL), need to be filled in by the respondents or by the researcher (if respondent are having difficulty to read and write).

## **2) The education program**

Referring to Table 3.4, during first meeting, the intervention group will be given with the self-efficacy enhancing program on foot self-care behaviour. The intervention is in a group seminar of education regarding knowledge on foot care to the respondents. The programs encompasses of several activities; 20 minutes of seminar presentation. The intervention or education content covered the following topics: awareness of risk factors and its complications, foot self-care behaviour including daily washing, inspecting foot for problems, moisturizing, wearing proper shoes and socks; toenail and feet care; and when to seek help from a healthcare professional. The demonstration is all about techniques of inspection and washes the feet as well as nail care. At the end of session, the researcher will encourage active role and leave the respondents to perform foot self-care behaviour independently. The intervention group will be participated with the series of weekly follow-up via appointments/ visits and/ or telephone call for up to 12 weeks. Meanwhile the control group are only will receive a usual health care.

In order to ensure compliance status of the respondents in intervention group, the respondents and the health care provider will be given a pamphlet regarding foot self-care behaviour for them to get more information on the topic itself. They are also will receive a folder/ chart to measure on the respondents' foot self-care behaviour daily. The health provider will be advised to remind the respondents about the foot self-care behaviour every day. A telephone call to the health provider will be done weekly till the end of intervention program. This is to measure the progress of self-care behaviour of the respondents.

## **3) Follow up**

A follow up session will be conducted at second meeting (four weeks after first meeting). In the intervention group, the respondents will be gathered in a group for a sharing and question and answer (Q & A) session. For respondents who manage to perform foot self-care behaviour effectively will be asked to be a mentor and share their skills and experiences with others. The objective of this session is to sustain the self-efficacy level of elderly with diabetes to continue performs foot self-care behaviour regularly. A specific guidance and motivation will be given individually if there is any respondent who do not able to perform foot self-care behaviour effectively. Whereas, the control group will only receive a regular visit from the researcher. Both intervention and control group will be assessed (second measurement) with the questionnaire (DFSBS, FCCS, FCOE, KFC, FS-QOL).

## **4) Evaluation (post-test)**

After two sessions (8 weeks) of the program, both the intervention and control group will be asked again to answer the questionnaire (KFC, FCCS, FCOE, DFSBS, FS-QOL) for evaluation of the effectiveness on the program. The foot self-care behaviour is a set of self-care activities that elderly with diabetes undertake to fulfil personal goals with regard to their disease. A time period of evaluation is referring to previous study by A time period of follow up and booster session is referring to previous studies by (Baba et al., 2014; Fan et al., 2013). Figure 3.3 illustrates the process of recruitment, intervention and the evaluation program. Table 3.4 describes the whole activities of the intervention program.

[figure not shown]

Figure 3.3 Flow chart of recruitment and the intervention program

Table 3.4 The whole activities of the intervention program

| Time                                | Activities                                                                                                                                                                                                                                                                                                                                                                                                                                                                                                                          | Mode of program                                                                                                                                                             | Duration                    |            |
|-------------------------------------|-------------------------------------------------------------------------------------------------------------------------------------------------------------------------------------------------------------------------------------------------------------------------------------------------------------------------------------------------------------------------------------------------------------------------------------------------------------------------------------------------------------------------------------|-----------------------------------------------------------------------------------------------------------------------------------------------------------------------------|-----------------------------|------------|
| Preliminary data/ assessment        | Screening
Blood sugar level testing (FBS)
Independence level (Katz Index)
Cognitive level (ECAQ)
Depression level (GDS)                                                                                                                                                                                                                                                                                                                                                                                          | Taking blood
Questionnaire                                                                                                                                               | 20 minutes                  |            |
|                                     | Consent form
The respondents need to fill in the questionnaire; demographic data, clinical characteristics, DFSBS, FCCS, FCOE, KFC, FS-QOL
Respondent will be randomly allocated                                                                                                                                                                                                                                                                                                                                              | Consent form
Questionnaire                                                                                                                                               | 20 minutes                  |            |
| Time                                | Activities                                                                                                                                                                                                                                                                                                                                                                                                                                                                                                                          |                                                                                                                                                                             | Mode of program             | Duration   |
|                                     | Intervention group                                                                                                                                                                                                                                                                                                                                                                                                                                                                                                                  | Control group                                                                                                                                                               |                             |            |
| First meeting
Time 1
(week 1) | The education program
For the elderly:
A group seminar regarding knowledge on foot care:
Awareness of risk factors and its complications, foot self-care behaviour: daily washing, inspecting foot for problems, moisturizing, wearing proper shoes and socks, toenail and feet care, when to seek help from a healthcare professional.
Note:
The health provider and the respondents will receive a pamphlet as a guidance and a checklist as a reminder in performing foot self-care behaviour daily | Usual health care                                                                                                                                                           | Power point presentation    | 20 minutes |
| Week 1, 2, 3                        | Follow up to the health provider                                                                                                                                                                                                                                                                                                                                                                                                                                                                                                    | None                                                                                                                                                                        | Phone call                  | 5 minutes  |
| Week 4                              | Visit, question and answer session, continuously give guidance and motivation on foot self-care behaviour. The respondents need to fill in the questionnaire; DFSBS, FCCS, FCOE, KFC, FS-QOL                                                                                                                                                                                                                                                                                                                                        | Regular visits. The respondents need to fill in the questionnaire; DFSBS, FCCS, FCOE, KFC, FS-QOL                                                                           | Discussion
Questionnaire | 20 minutes |
| Week 5, 6, 7, 8, 9, 10, 11          | Follow up to the health provider                                                                                                                                                                                                                                                                                                                                                                                                                                                                                                    | None                                                                                                                                                                        | Phone call                  | 5 minutes  |
| Week 12                             | Evaluation
Last visit. Keep reminding to maintain the foot self-care behaviour among the elderly
The respondents need to fill in the questionnaire; DFSBS, FCCS, FCOE, KFC, FS-QOL                                                                                                                                                                                                                                                                                                                                            | Evaluation
Last visit. Keep reminding to maintain the health care among the elderly
The respondents need to fill in the questionnaire; DFSBS, FCCS, FCOE, KFC, FS-QOL | Discussion
Questionnaire | 20 minutes |

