### 3.3 Study design

The design used for this research is a Randomized Control Trial (RCT) design with two groups; intervention and control, measurements will be completed before intervention and after intervention. In this single blind study, only the researcher is able to differentiate which group are under intervention or control group. The respondent will not be informed whether they are categorized under intervention or control group.

The intervention group will receive a self-efficacy enhancing program on foot self-care behaviour while the control group will receive a usual health care. The aim of the education program will that, after completed the program, the foot self-care behaviour, foot efficacy expectation, foot outcome expectation, knowledge on foot care and quality of life will be improved with respect to the program delivered. However, after the data collection process completed, the control group will be given the same program as the intervention group.

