### 3.5 Sample

#### 3.5.1 Sampling method

A probability cluster sampling with specific eligibility criteria will be used in this study. There are nine RSK in the Peninsular Malaysia. However, for the time being, RSK Negeri Sembilan was closed due to renovation process, so there are total eight of RSK in Peninsular Malaysia. RSK Cheras will be excluded for pilot testing and RSK Pengkalan Chepa located in West Peninsular Malaysia. Hence, six RSK will be allocated randomly using random sequence number generator where each group (RSK) is having equal chance to be neither in the intervention group nor control group. Here, there are three RSK will be taken in intervention group and another three RSK will be placed under control group. Figure 3.2 showed how the sample will be selected and grouped in this study.

[figure not shown]

Figure 3.2 Sampling selection process

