|---------------------------------------------------------------------------------------------------------------------------------------------------------------------------------------------------------------------------------------------------------------------------------------------------------------------------------------------------------------------------------------------------------------------------------------------------------------------------------------------------------------------------------------------------------------------------------|----|-------------|---------------------------------------|
| Honorarium
Study setting = RM100.00 x 8 RSK
Respondents = RM15.00 x 250 people
Research assistant = RM150.00 x 8 RSK

Printing / photocopy
Reading materials
RM2.00 x 250 (respondents and health provider)
Questionnaire (pilot study)
RM2.00 x 50 respondents = RM100 (x3 series of visit)
Questionnaire (real study)
RM2.00 x 250 respondents = RM500.00 (x3 series of visit)

Stationeries
Files, pen, pencil, A4 paper, envelope, staple, bullet, punch hole, eraser, liquid paper, CD |    |             | RM 800.00
RM 3750.00
RM 1600.00 |
| 7. Vote 35000 Peralatan dan aksesori
Equipment and accessories
Sila rujuk garispanduan untuk keterangan lanjut
(Please refer to guidelines for more information)                                                                                                                                                                                                                                                                                                                                                                           | NA | NA          | NA                                    |
| Bajet tahunan yang dicadangkan
Proposed yearly budget                                                                                                                                                                                                                                                                                                                                                                                                                                                                                                          |    | RM 7000.00  | RM 8000.00                            |

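### Table 3.4 allocates respondents where section 3.5.1 allocates homes, the timing of allocation is not stated, and the unblinded researcher who teaches also interviews some respondents on self-reported outcomes

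*Combined protocol and SAP*

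**What the plan says.** **Unit and timing of allocation.** Section 3.5.1 says "Hence, six RSK will be allocated randomly using random sequence number generator" and then that "there are three RSK will be taken in intervention group and another three RSK will be placed under control group". It gives no date for this step. In Table 3.4 the preliminary visit lists screening, consent and the baseline questionnaire, and then "Respondent will be randomly allocated".

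**Who knows the arm.** Section 3.3 calls the study single blind: "only the researcher is able to differentiate which group are under intervention or control group". Respondents are not told their group.

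**Who screens.** Section 3.7.2, part 1, describes screening in the passive, for example "All of them will be screen for glucose level", and names no assessor.

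**Who teaches.** Sections 3.7.1 (with Table 3.3) and 3.7.2, part 2, give this to the researcher, who is also to build a trusting relationship with respondents.

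**Who collects outcomes.** Respondents who read and write complete the questionnaires themselves (3.6.1). Otherwise the baseline set is filled in "by the researcher (if respondent are having difficulty to read and write", and section 1.7 says the researcher interviews those who cannot read or write. No separate or blinded outcome assessor is described. Appendix 6 contains "Research assistant = RM150.00 x 8 RSK", without a role.

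**The concern.** A respondent cannot be randomised individually if the whole home has been randomised, so one of the two statements must be wrong. Timing matters as well as the unit. When homes are allocated, everyone recruited in a home gets the same arm. If whoever recruits already knows that arm, it can influence who is approached and who enrols. With three homes per arm, such an influence would act on a large part of an arm at once.

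The second issue is measurement. The primary outcome is self-reported foot self-care behaviour. A respondent who is interviewed by the person who taught and encouraged that behaviour has a reason to report more of it. Control respondents were not taught by that person, so the two arms may not report on equal terms.

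**Working it through.** **1. The plan's sample size, reproduced.** Inputs from 3.5.2: means 32.32 and 36.22 (difference 3.90), SD 6.76, two-sided alpha 0.05, power 0.80, cluster size 6, intracluster correlation 0.05, dropout 20%.

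- n = 2 × 6.76² × (1.96 + 0.842)² / 3.90² = 47.18 (plan: 47 per group)
- Design effect = 1 + (6 − 1) × 0.05 = 1.25, and 47 × 1.25 = 58.75 (plan: 59)
- 59 × 1.2 = 70.8 (plan: 71), and 2 × 71 = 142 (plan: 142)

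The figure reproduces. Section 3.5.2 justifies the design effect by the cluster design, which fits allocation by home and not Table 3.4.

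**2. What the unit changes.** With 59 retained per arm:

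- Respondents allocated, no design effect: SE = 6.76 × √(2/59) = 1.245; 3.90/1.245 − 1.96 = 1.17; power about 0.88.
- Homes allocated: 118/6 = 19.7 per home; design effect = 1 + 18.7 × 0.05 = 1.93; SE = 6.76 × √(2 × 1.93/59) = 1.73; 3.90/1.73 − 1.96 = 0.29; power about 0.62. A t test on 4 degrees of freedom (three homes against three) gives about 0.41.
- If the intracluster correlation is instead assumed to lie between 0.01 and 0.10, power by home runs from 0.82 to 0.46 (normal), or 0.59 to 0.30 (t, 4 df).

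The cluster size of 6 used in 3.5.2 is a separate matter. The comparison here shows only that the two units describe different trials.

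**3. Timing, side by side.** Section 3.5.1 treats allocation as part of sampling and gives no date. Table 3.4 puts it last in the preliminary visit. Section 3.7.2 already separates the assessment visit from the education visit, so allocation between them is workable. Section 3.4.1 expects about 40–50 independent residents with diabetes per home, against a need for 142/6 = 23.7. Other exclusions will reduce that pool, but the text does not say which residents are taken if more qualify than are needed.

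**4. Roles, side by side.**

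| Task | Who, per the text |
|---|---|
| Knows the arm | Researcher only (3.3) |
| Screens | Not named (3.7.2, part 1) |
| Teaches | Researcher (3.7.1, Table 3.3, 3.7.2 part 2) |
| Interviews those who cannot read or write | Researcher (1.7; 3.7.2 part 1) |
| Research assistant | Budgeted, role not described (Appendix 6) |

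**5. Coaching and measurement together.** In Table 3.4 the intervention arm's week 4 visit combines guidance and motivation on foot care with the questionnaire, and week 12 combines a reminder to keep up foot care with it. Controls have ordinary visits and, at week 12, a general health reminder. Respondents who complete the form themselves are therefore also exposed. The text does not say which comes first within the visit.

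**6. Size.** The bias from interviewing would be (share interviewed × shift in reporting) in the intervention arm minus the same product in the control arm. The documents give neither the shares nor the shifts, so no figure follows.

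**The case against.** The strongest reply is that the allocation conflict is one loose table cell. The abstract, 3.5.1 and 3.5.2 all point to homes, and correcting the cell creates or removes no bias by itself. That stands. The cell still needs correcting, and the missing timing remains.

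Three stronger readings are tempting, and the documents do not support them.

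- *A reader might infer that the researcher screens while knowing the arm.* No screener is named. Section 3.7.2 invites all independent residents, and eligibility rests largely on scored instruments, blood glucose and health records, which limits discretion.
- *A reader might infer that selection bias is built in.* It arises only if the arm is known before enrolment. The one place that orders the steps lists allocation last. Figures 3.2 and 3.3, which may show the sequence, are not visible here and cannot be counted as silent.
- *A reader might put the bias at some fraction of the planned effect, or hold that analysis is powerless against it.* Any such fraction would be invented. Outcomes are measured at baseline and a mixed ANOVA over three times is planned, so imbalance visible at baseline can be partly addressed. Unmeasured selection and biased reporting cannot be adjusted for in that way.

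It is also fair that interviews cover only those who cannot read or write, that residents see no contrasting arm within their own home, and that control homes are visited too. These points narrow the reporting problem. They do not close it, because teacher and interviewer are the same unblinded person and coaching shares the outcome visits.

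**Conclusion.** The concern holds in limited form. Sections 3.5.1 and Table 3.4 contradict each other on the unit of allocation, and homes are clearly intended. Selection bias is possible, conditional on the arm being known before enrolment; the visible text neither establishes nor excludes that. Reporting bias is open under the plan as written, through interviews by the researcher who teaches and through coaching at the outcome visits. Its direction would plausibly favour the intervention, and its size cannot be estimated from the documents. The correction should be made because it is cheap. The conclusion rests on the readable text and assumes that the missing figures do not assign screening or outcome collection to someone else.

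**What to change.** 1. Change the allocation line in Table 3.4 to: 'RSKs (not respondents) are allocated 3:3 after screening, consent and baseline are complete in all six RSKs.' Make 3.5.1 say the same, and name who screens.
2. At weeks 4 and 12, collect the questionnaires before any coaching at that visit.
3. Have the research assistant, not the person who taught, conduct the week 4 and week 12 interviews from a fixed script, without being told the arm.
4. In 3.3, describe the blinding accordingly, and say that assistants may still infer the arm on site, since intervention respondents hold pamphlets and checklists.

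**Cost.** Mostly wording. The first seminar waits for the last home's baseline, and the interval from baseline to seminar may vary between homes, so it should be recorded. The assistant's time must be checked. Appendix 6 gives RM150 for each of 8 homes, which is 150 × 8 = RM1,200, while the amount that appears to belong to that line is RM1,600 (the table layout is uncertain). Nothing shows that either sum covers interviews at two visits.
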